### Intervention treatment

In addition to exergame training, EG participants will receive A-tDCS over the DLPFC, while CG participants will receive sham stimulation (S-tDCS) at the same site. Stimulation will be delivered using a battery-driven constant current stimulator with an LCD touchscreen (HDC progr), a portable stimulator (HDC stim), two cellulose sponge electrodes (7 × 5 cm) in saline bags, and conductive silicone electrodes. The anodal electrode will be placed over the left DLPFC (Brodmann area 46) using a positioning cap, and the reference electrode over the right shoulder. The DLPFC was chosen based on its established role in top-down cognitive control [20], conflict monitoring through anterior cingulate cortex connections [21], and evidence of improved working memory and executive function after A-tDCS in both healthy subjects [22] and PwMS [23]. Conductive gel will be applied under the electrodes to minimize impedance, which will be maintained below 5 kΩ. Only the tDCS operators will know the stimulation condition; participants and neuropsychological assessors will remain blinded. During each exergame session, A-tDCS will be applied online (concurrent with training) at 1.5 mA for 20 minutes, with a current density of 0.06 mA/cm², within established safety limits [4].

### Placebo treatment

In the sham condition, stimulation will be delivered for 30 seconds at the beginning and end of each 20-minute session, producing the typical tingling sensation under the electrodes while preventing sustained cortical modulation. This procedure makes sham indistinguishable from active stimulation, ensuring participant blinding.

### Timeline

Outcome measures will be administered at baseline, after the 10 treatment sessions, and at 1-month and 6-month follow-ups. The study duration is estimated at 2 years (Fig 1).

**Fig 1 pone.0337405.g001:**
[figure not shown]
Participant timeline according to the SPIRIT 2025 guidelines.

The schedule displays enrollment, randomization, interventions (A-tDCS + exergames; sham tDCS + exergames), and timing of cognitive and secondary outcome assessments at baseline, end of treatment, 1-month, and 6-month follow-ups. Figure adapted from Chan et al., BMJ 2025 (Creative Commons Attribution License).

Patient enrollment began in September 2024 and is expected to be completed by January 2026. Data collection should be finalized by July 2026, and data analysis is anticipated to be completed by September 2026.

### Statistical analysis and sample size

Descriptive characteristics of the included patients will be presented as mean ± standard deviation (SD) or median and interquartile range (IQR) for continuous variables and as absolute frequencies and percentages for categorical variables. Baseline characteristics of the patients will be also shown splitting the patients into the two groups of treatments and comparisons will be performed using Chi-squared test of Fisher’s exact test (for categorical variables) and Mann-Whitney U test or t-test (for continuous variables). Results of the SDMT and PASAT tests will be presented over time as Mean ± SD by showing separately the two groups of treatment. The repeated measures ANOVA will be used to assess the effect of treatment, the effect of time, and the interaction effect between time and treatment on the performance of the SDMT and PASAT tests. The sample size was calculated fixing a power of 0.80 and a significance level of 0.05 and we calculated the sample sizes required for between effect, for within effect and for the between–within interaction effects for both the neuropsychological tests, planning of picking as our final sample size the largest one. To calculate sample sizes, means of measurements over time and covariance matrix for the repeated measures were defined for the SDMT and PASAT tests based on clinical expectations and on previous findings [24]. The largest sample size was the one required for the between effect in the analysis of PASAT test, leading to a sample size of 33 patients in each group to detect the treatment effect of magnitude δ = 0.35. This sample size is even more satisfactory for the SDMT test, where a smaller sample size was required. However, assuming a drop-out rate of 20%, we finally need to enroll in 80 subjects with 40 patients per treatment group. After performing the repeated measures ANOVA, in case of presence of differences, we also plan to compare means using paired t-test, adequately adjusting for multiple testing. In case of missing data over follow-up, a multiple imputation by chained equations approach will be used with 10 imputations. Additionally, we will also perform the same analyses, using complete data to check the robustness of the results. A p value less than 0.05 will be considered significant. All the analyses will be conducted with the Statistical Software Stata version 16.0 (Stata Corporation, College Station, TX, USA). Randomization will be performed using computer-generated random numbers.

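### The planned repeated-measures ANOVA names no baseline covariate, and the between effect that sets the sample size averages over visits; a baseline-adjusted post-treatment contrast would be more precise at no extra cost

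*Protocol article*

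**What the plan says.** The Timeline section gives four assessments, the first before treatment: "Outcome measures will be administered at baseline, after the 10 treatment sessions, and at 1-month and 6-month follow-ups".

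Under Statistical analysis and sample size, the model for SDMT and PASAT has three terms: "The repeated measures ANOVA will be used to assess the effect of treatment, the effect of time, and the interaction effect". No baseline covariate is named. Baseline appears only in descriptive tables and in tests comparing the arms. None of the three ANOVA effects is named as the confirmatory one, and the planned follow-up comparisons of means are paired t-tests.

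The sample size section computed the "sample sizes required for between effect, for within effect and for the between–within interaction effects for both the neuropsychological tests" and took the largest. It reports: "The largest sample size was the one required for the between effect in the analysis of PASAT test". The result of that calculation is worded as "leading to a sample size of 33 patients in each group to detect the treatment effect of magnitude δ = 0.35". The inputs are described ("means of measurements over time and covariance matrix for the repeated measures were defined for the SDMT and PASAT tests") but their values are not printed. The article does not say outright whether baseline is a level of the time factor, or which visits δ = 0.35 refers to.

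**The concern.** The aim is a benefit of active stimulation after treatment, and the stated hypothesis is that both arms improve and the experimental arm improves more. That is an arm difference at the post-treatment visits, given where patients started.

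The between effect in a repeated-measures ANOVA is something else. It is the arm difference averaged over every visit in the model, tested against between-patient variance. With baseline as a level, one of the four visits is one at which randomisation makes the expected difference zero. The effect is diluted, a chance baseline imbalance enters the estimate, and the stable differences between patients stay in the error term. Without baseline as a level the dilution goes, but so does any use of the baseline score.

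At stake is precision. The trial already collects a measurement that could sharpen the arm comparison, and the effect that sizes the trial does not use it for that purpose.

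**Working it through.** **Inputs from the article.** Power 0.80, significance level 0.05, δ = 0.35, 33 per group (N = 66), one visit before treatment and three after.

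**Assumptions (the covariance matrix is not given).** SD of one score = 1; equal correlation ρ between all visits; no expected arm difference at baseline; constant difference D at the three later visits.

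**Step 1: reproduce the stated size.** Take δ as effect SD over error SD, so that for two groups the standardised difference in visit-averaged means is 2δ = 0.70. The noncentrality is λ = N δ² = 66 × 0.1225 = 8.085 on F(1, 64), which gives power 0.7997. The stated 33 is therefore reproduced to rounding (34 is the first size with strictly 80% or more). Reading 0.35 as a standardised mean difference would need 129 per group, so that is not what was used.

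**Step 2: the three candidate tests, with baseline as a level.**
- Treatment main effect: effect 0.75 D; variance of the four-visit mean v4 = (1 + 3ρ)/4; λ = (N/4)(0.75 D)²/v4 on F(1, 64).
- Treatment-by-time interaction: λ = (N/4)(0.75 D²)/(1 − ρ) on F(3, 192). Here 0.75 D² is the sum of squares of (0, D, D, D) about its mean.
- Baseline-adjusted mean of the three follow-ups: effect D; variance va = (1 + 2ρ)/3 − ρ²; λ = (N/4)D²/va on F(1, 63).

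For ρ = 0.7: v4 = 3.1/4 = 0.775 and va = 0.80 − 0.49 = 0.31. The λ needed for 80% power is about 8.09 for the two 1-df tests and 11.13 for the 3-df test. With N/4 = 16.5:
- main effect: D = √(8.09 × 0.775 / (16.5 × 0.5625)) = 0.82
- interaction: D = √(11.13 × 0.3 / (16.5 × 0.75)) = 0.52
- baseline-adjusted: D = √(8.09 × 0.31 / 16.5) = 0.39

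D detectable with 80% power at 33 per arm, in SDs of one score:

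| ρ | Main effect | Interaction | Baseline-adjusted |
|---|---|---|---|
| 0.5 | 0.74 | 0.67 | 0.45 |
| 0.7 | 0.82 | 0.52 | 0.39 |
| 0.8 | 0.86 | 0.42 | 0.33 |
| 0.9 | 0.90 | 0.30 | 0.25 |

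**Step 3: relative efficiency against the main effect.** This is v4/(0.5625 va): 1.90 at ρ = 0.3, 2.67 at 0.5, 4.44 at 0.7 and 6.67 at 0.8.

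**Step 4: if baseline is not a level.** The between effect is then the unadjusted mean of three follow-ups, with variance (1 + 2ρ)/3. Adjusting for baseline is still 0.667/0.417 = 1.6 times as efficient at ρ = 0.5, and 0.867/0.227 = 3.8 times at ρ = 0.8.

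**Step 5: power at the planning effect.** It depends on what δ = 0.35 stands for.
- Four-visit average including baseline: the implied D is 0.70 √v4 / 0.75, that is 0.74 at ρ = 0.5 and 0.82 at ρ = 0.7. Power is 80% for the main effect at both; 87.6% and 99.6% for the interaction; 99.5% and above 99.9% for the baseline-adjusted contrast.
- Post-treatment mean only, but analysed with baseline as a level: over ρ = 0.3 to 0.8, main-effect power falls to 60.5% down to 56.4%, against 86.7% to above 99.9% with adjustment.

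**The case against.** The strongest reply is that the plan does use baseline. With baseline as a level, the interaction tests whether the arms differ in change over time and removes stable between-patient variance. It is a planned test and was sized, and by the article's account it needed no more patients than the between effect. No effect is named as confirmatory, and taking the largest of several sizes is conservative. All of this stands, so a reader who infers that the ANOVA never adjusts for baseline goes further than the text allows. What remains is that the interaction spends 3 df on an omnibus question, gives no single treatment estimate, and is less powerful than the baseline-adjusted contrast at every ρ from 0.3 to 0.9 in these calculations.

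A reader might also infer that the stated power is false, or that most of the power is wasted. Neither follows. If the means entered in the calculation already had equal baselines, the dilution is inside δ and the 80% is right; the loss against the adjusted contrast is then about 17 to 20 points for ρ = 0.3 to 0.8. The larger drop in Step 5 needs a reading of δ that the article does not give. In information terms the loss passes one half only when ρ exceeds about 0.35.

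Nor is the main effect invalid. It is a correct test under the null and unbiased for the visit-averaged difference; it understates only the post-treatment difference. A sphericity correction is the kind of detail an article leaves to the analysis plan, and its absence is not counted here.

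**Conclusion.** The point holds as a free improvement, not as an error that invalidates the plan. The effect that sets the sample size is either diluted to three quarters of the post-treatment difference (baseline a level) or ignores the baseline score (baseline not a level). Both readings leave precision unused. At 33 per arm with ρ from 0.5 to 0.8 and baseline as a level, a baseline-adjusted contrast detects 0.45 down to 0.33 SD, where the main effect needs 0.74 up to 0.86 and the interaction 0.67 down to 0.42. The main effect then discards about 63% to 85% of the information (1 − 1/2.67 and 1 − 1/6.67).

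These sizes rest on equal correlations, a constant post-treatment difference and values of ρ that the article does not supply. The direction does not depend on the exact ρ within 0.3 to 0.9. The stated 80% power is not contradicted if δ = 0.35 is the four-visit average.

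**What to change.** 1. For SDMT and PASAT, make the confirmatory comparison the baseline-adjusted arm difference over the three post-treatment visits. Use either ANCOVA of the follow-up mean on baseline, or a mixed model on the post-treatment visits with baseline score, arm, visit and arm-by-visit. Report the estimate with a 95% CI.
2. Keep the repeated-measures ANOVA as a supportive analysis, and state whether baseline is one of its levels.
3. State whether δ = 0.35 refers to the four-visit average or to the post-treatment visits, and give the means and covariance matrix behind it.

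The cost is wording, settled before the allocation is revealed to those who analyse the data. By the article's own rule, an important modification also goes to the ethics committee and the registry. No new data, visits or patients are needed.

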### Participants

Participants will be recruited from the outpatient services of the Department of Neurology, ASL3 Genoa, the AISM Liguria Rehabilitation Service, and the Neurorehabilitation Unit of IRCCS Ospedale Policlinico San Martino, Genoa. Inclusion criteria are: (1) diagnosis of MS according to McDonald’s criteria [16]; (2) age between 18 and 60 years (to minimize potential age-related CI); and (3) Expanded Disability Status Scale (EDSS) score ≤7.5 [17]. Exclusion criteria include major psychiatric disorders, epilepsy, previous brain surgery, MS relapse requiring steroid therapy within the past two months, and bilateral visual acuity <6/10.

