### Methodology

Participants will be randomized into two groups: 40 in the experimental group (EG) and 40 in the control group (CG), matched for demographic characteristics (sex, age), EDSS score, and disease duration. All participants will undergo cognitive training using the Neurotablet system, a virtual-reality–based platform incorporating exergames for motor and cognitive rehabilitation. The system includes exercises with adjustable difficulty levels, enabling tailored treatment plans based on individual disability. The rehabilitation program will consist of 10 sessions (1 hour each), delivered 5 days per week for 2 consecutive weeks.

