
### Oversight and monitoring

The IRCCS Ospedale Policlinico San Martino, Genoa, will act as coordinating center, responsible for trial oversight, central randomization, data management, monitoring, and communications with the ethics committee and trial registry. Participants will be recruited at three sites (ASL3 Neurology Department, AISM Liguria Rehabilitation Service, and IRCCS Policlinico San Martino). Each site will have a principal investigator responsible for local conduct. A Steering Committee (PI, site PIs, statistician, data manager) will oversee scientific and operational aspects, including protocol amendments, recruitment, adherence, and data quality. Data will be entered into password-protected eCRFs stored on a secure institutional server, with anonymization, restricted access, and regular back-ups. Given the low-risk nature of the trial, no Data Monitoring Committee is planned; safety will be overseen by the PI and site PIs and reported to the ethics committee.

Participants will be withdrawn in case of intolerable adverse events, clinical worsening requiring treatment changes, participant request, or investigator decision for safety. Stimulation parameters will not be modified during the trial. Adherence will be promoted through flexible scheduling, continuous support, and the engaging use of exergames.

Unblinding is not anticipated but may be authorized by the PI in exceptional safety-related circumstances. In case of discontinuation or deviation, all scheduled outcome data (clinical, neuropsychological, and patient-reported) will continue to be collected and included in intention-to-treat analyses.

All adverse events (AEs), whether solicited or spontaneous, will be documented; minor AEs will be managed immediately, while serious/unexpected AEs will be reported promptly to the PI and ethics committee. Any important protocol modifications will be submitted for ethics approval and updated in the trial registry.

Personal data will be collected only for study purposes, stored securely, and anonymized for analysis/publication. The final dataset will be accessible to the PI and study team only; the sponsor has no restrictions on access. No specific ancillary or post-trial care is planned; clinical needs will be managed as per standard practice. Given the minimal risk profile of tDCS and exergames, no specific compensation beyond national regulations is planned.

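### Patients are recruited at three sites, but the stated ANOVA has no site term; adding one is a nearly free gain in precision, and its absence does not invalidate the test.

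*Protocol article*

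**What the plan says.** Oversight and monitoring names the sites: "Participants will be recruited at three sites (ASL3 Neurology Department, AISM Liguria Rehabilitation Service, and IRCCS Policlinico San Martino". It adds: "Each site will have a principal investigator responsible for local conduct". The Participants section describes the same three sources: a neurology outpatient department, a rehabilitation service run by an MS association, and a hospital neurorehabilitation unit.

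On allocation, Methodology says that the 40 patients per arm will be "matched for demographic characteristics (sex, age), EDSS score, and disease duration". Statistical analysis and sample size adds only this: "Randomization will be performed using computer-generated random numbers". Oversight and monitoring makes the coordinating centre "responsible for trial oversight, central randomization, data management, monitoring". Stratification by site is neither stated nor ruled out.

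On analysis, Statistical analysis and sample size says: "The repeated measures ANOVA will be used to assess the effect of treatment, the effect of time, and the interaction effect between time and treatment", for the SDMT and PASAT. The sample size was set by "fixing a power of 0.80 and a significance level of 0.05". The largest requirement was for the between-patient treatment effect on PASAT: 33 per arm for an effect of 0.35.

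**The concern.** The between-patient treatment effect on PASAT is tested against the variation between patients within an arm. If the three sites differ in average level, for whatever reason, that difference is part of this variation unless site is in the model. If one arm also happens to hold more patients from a high-scoring site, the difference between arms shifts and nothing in the stated model adjusts for it.

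The sizing effect sits at its 80% target with nothing to spare. Site is known for every patient without further data collection. The article names both the balancing factors and the effects to be assessed, and site is in neither list. The model as published would therefore give up whatever precision site could offer.

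**Working it through.** **Inputs from the article.** Three sites; power 0.80; significance level 0.05; effect 0.35 for the between-patient PASAT comparison; 33 per arm, so N = 66.

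**Input not in the article.** The share r of the between-patient error variance that site explains. It is assumed, from 0 to 0.20.

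**1. Reproduce the plan's figure.** Read 0.35 as Cohen's f, so that the two-arm standardised difference is 2 × 0.35 = 0.70. The normal-approximation formula for two means then gives 33 per arm. By the F test, the non-centrality is N × f² = 66 × 0.1225 = 8.085 on 1 and 64 degrees of freedom, and power is 0.7997. Reading 0.35 as a standardised mean difference would need 129 per arm, so the f reading is the one that fits.

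**2. Add site, arms balanced within site.** Site takes 2 degrees of freedom (64 becomes 62) and removes a share r of the error variance. The non-centrality becomes 8.085 / (1 − r).

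| r | Non-centrality | Power without site | Power with site |
|---|---|---|---|
| 0 | 8.085 | 0.800 | 0.799 |
| 0.02 | 8.250 | 0.800 | 0.807 |
| 0.05 | 8.511 | 0.800 | 0.819 |
| 0.10 | 8.983 | 0.800 | 0.839 |
| 0.20 | 10.106 | 0.800 | 0.879 |

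The column without site is constant because 0.35 is defined against the total error SD, site variation included.

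**3. Add site, allocation that ignores site.** Some of the treatment contrast is then confounded with site by chance. The expected loss is 2 / (N − 1) = 2/65, about 3.1%, so the non-centrality is multiplied by 63/65. Power with site becomes 0.787, 0.795, 0.807, 0.828 and 0.869 for r = 0, 0.02, 0.05, 0.10 and 0.20. Adjustment breaks even at r of about 3%. A simulation of 20,000 trials with three sites of 22 patients agrees in pattern: 0.783 with site against 0.799 without at r = 0, and 0.865 against 0.799 at r = 0.20.

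**4. Validity of the test without site.** In the same simulation, type I error without site was 0.050, 0.048, 0.048 and 0.054 for r = 0, 0.05, 0.10 and 0.20.

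**5. How large chance imbalance could be.** Suppose 80 patients are allocated 40:40 without regard to site. For assumed site sizes of 27/27/26, 40/25/15 and 50/20/10, the share of some site differs between arms by 20 percentage points or more in 17%, 15% and 15% of allocations. If that site's mean differs from the others by 0.5 to 1.0 SD (assumed), the arm difference shifts by 0.20 × 0.5 = 0.10 to 0.20 × 1.0 = 0.20 SD. Against the planned 0.70 SD, that is 14% to 29%. In a small site the effect is slight: an 8:4 split in a 12-patient site that differs by 0.5 SD shifts the difference by 0.5 × 4/40 = 0.05 SD.

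**The case against.** The strongest reply is that this is an article, that stratification factors and a centre covariate are often left to the full protocol or analysis plan, and that listing the effects to be assessed does not say no other term will be fitted. That has force, and it is one reason the point is minor. It does not remove it: the article sets out its model effects and its matching factors, and site is absent from both.

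A second reply is that no shortfall against the planned power is shown. This stands. Power without site is 0.80, as planned; site can only add to it, by an amount that the documents do not let us know. If site explains 2% or less, the gain is under one point with balanced arms, and there is a small loss if allocation ignored site.

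Three stronger readings are tempting, and the documents support none of them.
- A reader might infer one unstratified random list. The text says only that randomisation is central and computer-generated, and it also speaks of matching on four factors. The imbalance figures above are therefore conditional on an allocation that ignores site.
- A reader might infer that case mix differs between sites. The types of service make that plausible, but it is not stated, and all sites share the same eligibility criteria.
- A reader might infer that training and testing are delivered separately at each site. The article speaks of recruitment and of local conduct, and goes no further.

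Nor does chance imbalance bias the comparison. Under randomisation it is sampling error that the standard error already reflects, as the simulated type I error shows. If allocation was in fact stratified by site, leaving site out makes the test conservative, which is again a loss of precision.

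**Conclusion.** The point holds as a minor matter of precision. Three sites recruit, the stated model has no site term, and so between-site variation stays in the error of the test that sizes the trial and chance site imbalance is left uncorrected. With arms balanced within site, including site changes power at 66 patients by between −0.0004 (site explains nothing) and about +8 points (site explains 20%). If allocation ignored site, the range is about −1 to +7 points.

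This rests on three assumptions: that 0.35 is Cohen's f, which reproduces 33 per arm; that 33 per arm are analysed; and the range taken for r, for which the documents give no figure. It should not be read as an invalid test, a biased estimate or a faulty randomisation.

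**What to change.** In Statistical analysis and sample size, before analysis begins, add site (three levels) as a fixed between-patient factor in the SDMT and PASAT models. Do this in both the multiply imputed and the complete-data analyses, and include site in the imputation model so that the two steps agree. State in the same place whether randomisation was stratified by site. A site-by-time term is optional, and the allocation need not change.

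The cost is a sentence or two of wording and 2 of 64 between-patient degrees of freedom, plus about one point of power if allocation ignored site and sites turn out not to differ. No extra patients or data are needed. The article expects data collection to end in July 2026 and analysis in September 2026. The term should be fixed before results are seen, because adding it afterwards would be open to challenge.

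### Enrolling 40 per arm with 20% drop-out leaves 32 per arm, one short of the 33 the plan says it needs

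*Protocol article*

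**What the plan says.** All the figures are in the protocol article, under Statistical analysis and sample size.

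- Error rates: "The sample size was calculated fixing a power of 0.80 and a significance level of 0.05".
- Comparison that sets the size: "The largest sample size was the one required for the between effect in the analysis of PASAT test".
- Required number: "leading to a sample size of 33 patients in each group to detect the treatment effect of magnitude δ = 0.35".
- Allowance for loss: "assuming a drop-out rate of 20%, we finally need to enroll in 80 subjects with 40 patients per treatment group".

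The Abstract and the Methodology section repeat 40 per arm. The formula that takes 33 to 40 is not given.

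Two further statements bear on what a drop-out costs. The sample-size section says: "In case of missing data over follow-up, a multiple imputation by chained equations approach will be used with 10 imputations", with an analysis of complete data as a robustness check. Oversight and monitoring says that, after discontinuation or deviation, scheduled outcome data "will continue to be collected and included in intention-to-treat analyses".

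**The concern.** The only purpose of the inflation step is to have 33 patients per arm left after the assumed loss. At the assumed loss it leaves 32. The required number, the drop-out rate and the enrolled number therefore cannot all be right.

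The PASAT between-group comparison gave the largest requirement of those calculated, so it has no spare margin below 33. At stake is whether the article's design justification, 80% power with room for 20% drop-out, is true as written. A final report that repeats it would carry the error forward.

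**Working it through.** **Inputs** (all from Statistical analysis and sample size): 33 per arm required, δ = 0.35, power 0.80, significance level 0.05, drop-out 20%, 40 per arm enrolled.

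**Step 1. Reproduce the 33 per arm.** The article does not define δ. I take it as the standardised between-effect size of an analysis of variance with two equal groups. The test is then F with 1 and N − 2 degrees of freedom and noncentrality λ = N × δ².

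- N = 66: λ = 66 × 0.1225 = 8.085, power 0.7997, which is the stated 80% after rounding.
- Cross-check: a two-sided comparison of two means with standardised difference 2 × 0.35 = 0.70 (normal approximation) also needs 33 per arm.
- Reading 0.35 itself as the standardised mean difference would need 129 per arm, so that is not what was done.

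**Step 2. Reproduce the 40 per arm.**

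- Multiplying: 33 × (1 + 0.20) = 39.6, rounded up to 40. This matches the plan.
- Dividing: 33/(1 − 0.20) = 41.25, rounded up to 42 per arm, 84 in total. Rounding only the total gives 66/0.80 = 82.5, so 83.

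The division is correct, because 20% is lost from those enrolled, not from those retained.

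**Step 3. What 40 per arm delivers.**

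- Retained at 20% loss: 40 × 0.80 = 32 per arm, 64 in total, against a target of 66.
- Largest loss that still leaves 33: 1 − 33/40 = 17.5%.
- Shortfall in enrolment: 84 − 80 = 4 patients.

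**Step 4. Effect on power among completers.**

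| Per arm | F test, δ = 0.35 | Normal approximation, d = 0.70 |
|---|---|---|
| 32 | 0.7871 | 0.7996 |
| 33 | 0.7997 | 0.8115 |

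The loss is 0.7997 − 0.7871 = 0.0126 on the F test and 0.8115 − 0.7996 = 0.0119 on the normal approximation.

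**Step 5. Sensitivity to rounding of δ.** If the true input lay anywhere from 0.345 to 0.3549, F-test power runs from 0.7883 to 0.8105 at 33 per arm and from 0.7755 to 0.7981 at 32. At either end the loss is 1.2 to 1.3 percentage points.

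**The case against.** The strongest reply is that this hardly matters. The gap is one patient per arm and little more than one point of power. The 33 itself rests on means and a covariance matrix taken partly from clinical expectation, and uncertainty in those inputs may well exceed one point. That is fair and it limits the consequence. It does not make the three figures agree.

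A second reply is that drop-outs are not a total loss. Missing follow-up is to be multiply imputed, data collection continues after discontinuation, and a patient lost before month 6 has already supplied earlier assessments to a between-group comparison over four time points. This also stands in part: the 64 patients describe the complete-data check more closely than the main analysis. But imputation does not restore outcomes that were never observed, and the plan's own inflation step treats drop-outs as lost. On that basis it misses its own target.

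Third, the 78.7% depends on how δ is read, and the normal approximation puts 32 per arm at 79.96%. The exact power is therefore uncertain within about 79% to 80%. The count of 32 against 33 is not.

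Finally, multiplication by 1.20 is inferred. Rounding 82.5 down to a convenient 80 would give the same figure, so the cause is probable rather than shown. Whichever it was, 80 is too few for the stated allowance.

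**Conclusion.** The concern holds. With 40 per arm and 20% drop-out, 32 per arm remain, one below the stated requirement; 42 per arm (84 in total) would be needed to keep 33. This follows from the plan's own numbers and rests on no assumption about δ.

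The size is modest: two patients fewer than the 66 required, and F-test power among completers of 78.7% instead of 80.0%. The power figure assumes that δ is the effect size that reproduces 33 per arm and that drop-outs contribute nothing. The planned imputation and continued data collection may make the actual loss smaller. It is an error in a figure that the design relies on, not a sign of a seriously underpowered trial.

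**What to change.** Keep 80 patients and correct the sentence in Statistical analysis and sample size in one of two ways:

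- state that 40 per arm retains the required 33 provided drop-out is at most 17.5%; or
- keep the 20% allowance and state that 32 per arm would then remain, with power of about 79% among completers, naming the test and the definition of δ behind that figure.

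The cost is one sentence and a slightly less favourable drop-out allowance or power. No patients are added, and the design and the analysis do not change. Enrolling 42 per arm would also reconcile the figures, at the cost of 4 more patients. With enrolment open since September 2024 and due to close in January 2026, a gain of about one point of power hardly justifies that. The correction should be made before the results are analysed, so that the final report states the power actually planned for.
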